#### Random assignment of students in HOPS schools to school or research provider.

Students randomly assigned to the HOPS condition will be randomized once again to receive HOPS from either a school provider or research provider (on a 1:1 basis). The sequence of assignment of students in the HOPS condition to the school or research provider will be determined by a separate computer-generated list of random identification numbers overseen by the team statistician. Caregivers and teachers will be informed about study assignment after caregiver consent and child assent is provided.

#### Concealment.

Given that the study is a pragmatic trial being conducted under real-world conditions, no attempt will be made to conceal treatment assignment from caregivers, students, teachers, and intervention providers. In addition, study team members will be fully aware of treatment assignment.

#### Collection of outcome data.

Outcome data for students in HOPS and TAU-WL will be collected at baseline and post-treatment (about 4 months after baseline). Follow-up data will be collected 6 months after baseline for students assigned to the HOPS condition. In addition, follow-up data will be collected 12 months after baseline for students in HOPS who remain in their school of enrollment the following school year. We will not collect 6-month and 12-month follow-up data for students in TAU-WL because of ethical concerns about further delaying the delivery of HOPS to those in the control group. However, we will collect post-treatment outcome data after students in the TAU/WL condition receive the HOPS program. Treatment fidelity, student engagement, and parent engagement will be assessed for participants in the HOPS condition during the intervention period. Provider-student working alliance will be assessed after the intervention period. Severity of organization problems, ADHD symptoms, disruptive behavior symptoms, and anxiety symptoms, as well as school organizational factors that may contribute to intervention implementation, will be assessed at baseline. (See Fig 3 for the study plan and flow diagram and see Fig 1 for a list of measures and the timelines for administering measures).

**Fig 3 pone.0343894.g003:**
[figure not shown]
Study plan and flow diagram. The figure depicts random assignment to HOPS and TAU/WL, random assignment to school vs. research provider for participants in HOPS, and data collection at four time periods. HOPS-ST refers to HOPS implemented by a school team member, and HOPS-RT is HOPS implemented by the research team.

### Research settings

The study will be conducted in Philadelphia, PA greater metropolitan region. Our team will purposely recruit schools that are highly diverse in subsidized lunch rates of the schools and racial and ethnic composition of the students to maximize generalizability. Our team will attempt to recruit schools with varying levels of urbanicity (i.e., rural, suburban, and urban). We expect the racial and ethnic minority composition across schools to range from 15% to 99% and subsidized lunch rates to range from 15% to 100%. For each school, we plan on recruiting one or two school providers to implement the HOPS intervention.

### Student participants

Students will be eligible for this study if: (a) they attend a school participating in the study, (b) they are enrolled in grades 6–8 and placed in general education for a majority of the day, and (c) they are identified as having OTMP deficits that are impairing academic performance, as identified by the four interference items on the Children’s Organizational Skills Scale-Teacher version (COSS-T; [22]). Students classified with emotional/behavioral disorders and/or learning disabilities will be included if it is determined that the students’ disabilities are being addressed adequately in their current educational program and OTMP skill deficits are a primary concern. Students with a one-to-one aide will be excluded because the presence of an aide substantially alters how an organizational intervention is implemented. In addition, students from families in which both caregivers do *not* speak English will be excluded because the program has not yet been developed for non-English speakers. Parents or legal caregivers must give consent, and students must provide assent for student and family participation, which can be withdrawn at any time during study participation. The potential for harm to participants is minimal, but they are informed that it is possible they may feel uncomfortable in completing measures. Participants are not mandated to complete items on measures used in the study.

### Recruitment

Two primary methods will be used to recruit schools. First, emails will be sent to the principals of schools serving students in grades 6–8 located in the large metropolitan area in which the study will be conducted. The selection of schools will be inclusive of districts across the region to achieve balance across subsidized lunch rate levels of the schools (low [0%−30%], middle [31%−60%], and high [61%−100%]). In addition, there will be an intentional effort to recruit schools in urban, suburban, and rural areas. Second, emails will be sent to principals of schools from districts in which we have previously conducted research or those referred to us by school administrators or other researchers. Approval will be obtained from the school principal, school superintendent, and school board (as necessary) prior to conducting research in the school. In addition, principals will be asked to identify one or more school providers to implement the HOPS intervention. School provider(s) must provide consent to participate in the study for the school to be enrolled in the study. Once all approvals and consents are obtained from school professionals, the school will be randomly assigned to a study condition (HOPS vs. TAU/WL).

Students will be referred to the study by their classroom (general education) teachers. School principals will identify the specific strategies to be used in convening teachers, informing them about the study, and obtaining referrals. Teachers will be informed that referral of a student to the study indicates their willingness to complete forms for outcome evaluation. The pool of teachers selected for inclusion in the referral process will be asked to nominate students from their general education classroom: (a) who are struggling the most with OTMP skills, (b) whose OTMP skill deficits interfere with their academic performance, and (c) who have at least one caregiver who speaks English. Each teacher who agrees to participate will complete a nomination form for each referred student for the purpose of determining student eligibility.

After a student is referred and determined to be eligible, a professional from the school, typically the school provider, will attempt to contact the parent or legal guardian to explain the study, indicate their child has been referred for HOPS through the study, and determine if the family is willing to be contacted by the study team. The school professional will often send a letter to the parent/guardian that includes a link to an electronic survey to offer permission for the study team to contact the family and provide contact information. The school provider may also contact (phone or email) parent(s)/guardian(s) of identified students to introduce the study. When the school gets permission from a family to share contact information with the study team, they will pass that information to the study team. With caregiver approval, a member of the study team will contact the family to determine interest, obtain caregiver consent, and obtain student assent.

### Intervention conditions

The study has two intervention conditions: HOPS intervention implemented by a research or school provider and TAU/WL.

#### HOPS program.

HOPS includes 16 sessions with the student, each about 20 minutes long. HOPS has three components: (1) materials organization, (2) homework management, and (3) time management. In addition, the program includes two caregiver consultations and, when feasible, one teacher consultation to inform them how they can support implementation of HOPS strategies at home and school. In this study, HOPS will be implemented by a school provider or research provider. The school provider can be a teacher (general or special education) or member of the student support staff (e.g., school counselor, school psychologist). The research provider will be a member of the research team with experience in special education, school psychology, counseling, or education research.

***Materials Organization Component:*** Developing an efficient and structured system for managing school materials is a major goal of HOPS. During the first week of the program, students work with their provider to establish a system of backpack, binder, and computer files organization. An organization checklist, consisting of operationalized criteria for backpack, binder, and computer files organization is utilized. Baseline organization is recorded on the first session, and an organization system based on the checklist is established during the second session. The organization checklist is completed at every following intervention session during the program. Intervention providers work with students to develop strategies for maintaining their materials organization system.

***Homework Recording and Management Component:*** The goal of this component is for students to establish a structured system for keeping track of and managing homework assignments. Students use a planner or calendar where they record all of their homework assignments and upcoming tests. Even if this information is available on different teacher websites, students transfer that information to their planner so they can see it all in one place and learn to plan ahead. Accuracy of recording is checked and documented by the provider at each HOPS session. Students also maintain a homework folder in their school binder. All assignments to be completed or papers to be signed are placed on the left side of the folder, and all completed assignments to be turned in are placed on the right side. As part of the organization checks, intervention providers evaluate use of the homework folder to ensure that only current assignments are in the folder and all other work is filed in the appropriate section of the binder.

***Time Management Component:*** The goal of this component is for students to reduce procrastination by planning more effectively for the completion of long-term projects and tests. A time management skills checklist is utilized to guide implementation of time management strategies. The time management skills checklist includes operationalized criteria separated into two categories: (1) planning for upcoming tests and quizzes and (2) planning for projects. A tiered approach is used to ensure students master the most basic skills (e.g., recording a test in the planner) before attempting more complex skills (e.g., breaking test studying into smaller pieces).

#### TAU/WL.

Students in the TAU/WL condition will receive the supports for OTMP skills typically offered to students in their schools. Teachers will be asked to complete a questionnaire at baseline to determine the OTMP supports being received by each student. Students in this condition will receive the HOPS program from a school or research provider after post-intervention data have been collected, which could be in the spring of the year of enrollment or the following school year.

### Training and technical support for HOPS providers

Procedures for offering training and technical support for intervention providers were adapted from those used in prior studies of HOPS [4,10] and reflect the strategies used in actual practice by [name] and colleagues when school professionals request training to implement HOPS. School and research providers will receive a copy of the HOPS manual [9] and 1.5–2 hours of training before providing HOPS. The training will include a description of: (a) the conceptual model and core principles of HOPS, (b) principles for promoting behavior change, (c) major components of the program, (d) procedures for providing each student session, (e) procedures for providing parent consultation (and teacher consultation when feasible), and (f) guidelines for selecting reinforcers for students. The training is provided virtually by [name] or a trainee working under his direction.

Intervention providers will be able to login to a website (hopsintervention.com) that will give them access to videos of [name] providing HOPS training and responding to common treatment challenges, access to PowerPoint slides for [name] training, and responses to Frequently Asked Questions (FAQs). Through the website, intervention providers will be able to ask brief logistical/technical questions about HOPS, which will be answered regularly by the training team ([name] and trainees). In addition, intervention providers will be given the opportunity to receive consultations on demand via telephone, virtual communication, or email with this trainee. The training team will log each consultation call to record the name of the provider, topics discussed, and duration of communication.

### Outcome measures – Proximal and distal

The *Children’s Organizational Skills Scale – Parent and Teacher versions (COSS-P, COSS-T)* will be used to assess changes in OTMP functioning at home and school. COSS Total scores (26 items for COSS-P, 28 for COSS-T) have strong construct and discriminant validity [23] and treatment sensitivity [4]. Each item is rated on a 4-point scale. The total score will be used in analyses, with higher scores being less favorable.

The *Homework Problem Checklist (HPC)* is a 20-item caregiver-report measure that indicates the frequency of child homework problems. The HPC has been shown to have strong construct validity [24] and treatment sensitivity [4]. Each item is rated on a 4-point scale. The total score will be used in analyses with higher scores indicating more problems.

The *Homework Performance Questionnaire – Teacher version (HPQ-T)* assesses students’ homework behavior during the past 4 weeks. Each item is rated on a 7-point scale indicating how often each behavior occurs, with higher scores indicating better performance. The 17-item General factor that assesses overall homework competence has strong construct validity [25] and will be used in analyses.

The *Academic Proficiency Scale (APS)* is a teacher-report measure assessing proficiency in six academic subjects. Each item is rated on a 5-point scale (1 = well below standard expected at this time of year; 3=at standard; 5 = well above standard). This measure has high internal consistency [8] and strong treatment sensitivity [5]. The mean item score will be used in analyses, with higher scores indicating better performance.

Student *academic report card grades* will be used to examine the impact of HOPS vs. TAU/WL on academic performance. Student grades will be recorded for the last marking period of the year prior to enrollment (baseline), the year of enrollment (post-treatment), and the year following enrollment (follow-up). Grades will be harmonized across participating school districts to a uniform grading scale (ranging from a low of 1 to a high of 4). A composite academic grade score will be computed for each student based on their grades in math and reading/language arts (possible range = 1–4). Higher scores indicate better outcomes.

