## Materials and methods

### Trial design

#### Random assignment to study conditions and providers.

The study is a two-group, parallel randomized controlled trial that is designed to include about 30 schools. Random assignment will be conducted at the level of schools and will occur after the school grants approval and the school provider offers consent. The study has two arms: HOPS and TAU-WL. Schools will be stratified by subsidized lunch status (low, medium, high) and randomly assigned to HOPS or TAU-WL at a 2:1 ratio. The sequence of assignments to treatment conditions will be determined using a computer-generated list of random identification numbers, conducted by the study statistician to ensure an unbiased and unpredictable assignment of participants to the study arms. The list of random numbers is generated using the statistical software program R [21]. The study team will inform the principal and school provider after random assignment of the school to study condition has been made. The study is designed to compare HOPS to what students typically receive to address their OTMP skills deficits. A WL design was chosen to be responsive to feedback from school officials who expressed concerns about participating in the study if identified students were not able to obtain HOPS. Students in TAU/WL schools will receive HOPS later in the school year of enrollment or in the school year following the year of enrollment. Students enrolled in the highest grade level in the school (e.g., 8^th^ grade) will be enrolled in the first few months of the school year, so that there is enough time for them to receive HOPS before the end of the school year if their school is assigned to the TAU/WL condition. Students will be enrolled in this study during the period from 25/10/2021–28/02/2026.

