#### Analyses for Aims 1–3: Evaluation of HOPS vs. TAU/WL and comparison of HOPS-ST to HOPS-RT.

*Hypothesis 1:* Students in HOPS-ST will demonstrate significantly fewer OTMP skills deficits and homework problems and will show significantly better academic performance at post-treatment compared to students in TAU-WL*Hypothesis 2:* Students in HOPS-RT will demonstrate significantly fewer OTMP skills deficits and homework problems and will show significantly better academic performance at post-treatment compared to students in TAU-WL.*Exploratory:* Examine whether the effects of HOPS-ST and HOPS-RT differ at post-treatment and follow-up.

A linear mixed-effects modeling approach will be used to examine intervention effects at post-treatment. An intent-to-treat approach to data analysis will be applied, including all children with baseline data in the analytic model. Under this approach, we will examine differences between students in HOPS (for HOPS-ST and HOPS-RT separately) vs. TAU-WL (as well as for students in HOPS-ST vs. HOPS-RT) by fitting a multilevel model in which students are nested within schools. In addition to including an indicator variable for the treatment condition, we will include covariates that explain variation at the student and school levels. To explore the sustainability of the intervention effect, we will examine how both means and slopes (rates of change) vary from baseline to 6-month and 12-month follow-up using regression analyses. Changes in mean and slope reflect variations in the magnitude of effect and pace of change during different phases of the study.

Because the efficacy of HOPS will be evaluated on three different domains of outcome measures (organizational skills, homework performance, academic achievement), we will use a Bonferroni-adjusted significance level to correct for multiple comparisons within each domain. As a result, the significance level will be adjusted to.025 per domain for the two measures of organizational skills (COSS-P, COSS-T), the two measures of homework performance (HPC, HPQ-T), and the two measures of academic achievement (APS, academic grades).

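### The post-treatment report-card grade is taken at the end of the enrollment year, by which time some waitlist students will have started or finished HOPS

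*Protocol article*

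**What the plan says.** All places are in the protocol article.

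- **Outcome measures – Proximal and distal.** Report-card grades "will be used to examine the impact of HOPS vs. TAU/WL on academic performance". The timing is the same for every student: "Student grades will be recorded for the last marking period of the year prior to enrollment (baseline), the year of enrollment (post-treatment"), with a further grade from the year after enrollment as follow-up.
- **Collection of outcome data.** The general rule is different: "Outcome data for students in HOPS and TAU-WL will be collected at baseline and post-treatment (about 4 months after baseline"). Later data are not collected from TAU/WL, so as not to delay their HOPS further.
- **TAU/WL.** Waitlist students receive HOPS "after post-intervention data have been collected, which could be in the spring of the year of enrollment or the following school year".
- **Random assignment to study conditions and providers.** This agrees: "Students in TAU/WL schools will receive HOPS later in the school year of enrollment or in the school year following the year of enrollment". Students in a school's highest grade are enrolled in the first few months of the year "so that there is enough time for them to receive HOPS before the end of the school year if their school is assigned" to TAU/WL.
- **Analyses for Aims 1–3.** Grades are one of "the two measures of academic achievement (APS, academic grades"), each tested at .025. The analysis is intent-to-treat and includes all children with baseline data. Hypotheses 1 and 2 both predict better academic performance than TAU/WL at post-treatment.

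**The concern.** The rating outcomes are collected about 4 months after baseline, before waitlist students cross over. The grade is tied to the school calendar instead, and the end of the enrollment year can fall after crossover. A control student treated in the spring therefore contributes a grade that already carries some HOPS effect.

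If HOPS improves grades, the contrast is diluted, and a null result could be misread as HOPS failing to improve achievement. Grades are also the only academic outcome that is not a rating completed for the study; the APS comes from teachers who know the assignment.

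Aim 4 is affected as well. In an exposed control, the mediators are measured before HOPS and the grade is earned during or after it, so the grade can rise with no recorded change in the mediator.

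**Working it through.** **Timing, set side by side**

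1. The post-treatment grade is from the last marking period of the enrollment year, in both arms.
2. TAU/WL students may start HOPS in the spring of that year. For the highest grade, fitting HOPS into that year is the stated reason for enrolling early.
3. For those students, the grade in step 1 is earned during or after HOPS.
4. One might read the post-intervention data that must precede waitlist HOPS as including the grade. That grade is not complete until the year is ending, so spring delivery would then be impossible, yet two sections provide for it. The statements cannot all be followed.
5. Nothing in the article moves the grade window for TAU/WL students, or says how exposed controls are handled in the grade contrast.

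**Size (illustration only)**

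No stated figure is in dispute. Two quantities are assumed because the article gives neither: f, the share of TAU/WL students exposed by the last marking period, and g, the fraction of the benefit they have realised by then.

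Inputs from the power paragraph under Analyses for Aims 1–3: 20 HOPS and 10 TAU schools, ICC 0.04, R² 0.60 at both levels, α = 0.025 (taken as two-sided) and an MDES of 0.48. The sample is 135, or 122 after attrition. I use 135 × 0.9 = 121.5, that is 40.5 students in each of HOPS-ST, HOPS-RT and TAU/WL.

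Variance of HOPS-ST (or HOPS-RT) minus TAU/WL, in SD units:

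- school part: 0.04 × 0.40 × (1/20 + 1/10) = 0.0024
- student part: 0.96 × 0.40 × (1/40.5 + 1/40.5) = 0.0190
- total 0.0214, standard error 0.146

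With a noncentral t on 28 df, power at 0.48 is 81%, close to the stated 80%.

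Diluted effect = 0.48 × (1 − f × g):

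| f | g | Effect seen | Power |
|---|---|---|---|
| 0 | – | 0.48 | 81% |
| 0.15 | 0.5 | 0.44 | 75% |
| 0.15 | 1 | 0.41 | 66% |
| 1/3 | 0.5 | 0.40 | 64% |
| 1/3 | 1 | 0.32 | 44% |
| 1/2 | 0.5 | 0.36 | 54% |
| 1/2 | 1 | 0.24 | 25% |

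Setting the standard error so that 0.48 has the stated 80% power (27 df) gives nearly the same answers: 63% at f = 1/3, g = 0.5; 53% at f = 1/2, g = 0.5; and 24% at f = 1/2, g = 1.

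**The case against.** The strongest reply concerns extent, and much of it stands.

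- **Exposure is partial.** A reader might infer that the whole control arm is contaminated. The article does not support that. Waitlist students treated the following year have a clean enrollment-year grade, and only the highest grade is scheduled so that HOPS fits within the year. For a student enrolled as late as February, 4 months later is about the end of the school year, so the last marking period roughly matches the post-treatment assessment anyway.
- **The full-benefit rows are the worst case for their f.** Highest-grade controls wait about 4 months from enrollment and then have 16 sessions, so many could be mid-program in the last marking period. The article also treats academic performance as a distal outcome. The 44% and 25% figures should not be read as the expected loss. The 0.48 is the stated MDES, not a forecast for grades.
- **The follow-up grade.** A reader might infer that following-year grades form a second contaminated comparison. Hypotheses 1 and 2 contrast with TAU/WL only at post-treatment, and the 6- and 12-month assessments are not collected in TAU/WL. The stated purpose of grades is worded broadly enough to need one clarifying sentence, but no controlled follow-up test is planned.
- **Reach.** Grades are one of six outcome measures, the other five are unaffected, and Aim 4 is exploratory. If HOPS helps, the bias is toward no difference and would not manufacture a benefit.

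The timing conflict itself remains. Early treatment of highest-grade controls is planned, and the grade rule makes no allowance for it.

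**Conclusion.** The point holds for a subset of controls on one outcome. As written, the end-of-year rule places HOPS exposure inside the control grade of TAU/WL students treated in the enrollment year, and biases that contrast toward no effect.

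The direction rests on HOPS having some benefit on grades. The size cannot be fixed from the article, because f and g are both unknown. Over f from 0.15 to 1/2 and g of 0.5 or 1, a true 0.48 would appear as 0.44 down to 0.24, and power would fall from 81% to between 75% and 25%. The claims about COSS, HPC, HPQ-T and APS are not touched.

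**What to change.** Define the post-treatment grade in both arms as the marking period that closes nearest the 4-month assessment and before HOPS begins for TAU/WL students. Apply the same rule to HOPS students, matched by grade level and enrollment timing, so that both arms are graded over comparable periods.

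Keep the end-of-year grade as a sensitivity measure, with each TAU/WL student's HOPS start date recorded. Do not set overlapping control grades to missing: that removes data from one arm only, concentrated in the highest grade, and sits badly with the intent-to-treat rule. Add a sentence stating that following-year grades are not a comparison with an untreated control. Settle the definition before the grade comparison is run, so that the choice of window cannot look data-driven.

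The cost is about one paragraph. It assumes that school records show each marking period, which the article does not say. The earlier period may also overlap HOPS delivery for treated students and dilute their effect somewhat; the sensitivity analysis helps to show how much the choice of window matters.
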